# The inclusion of mobilisation with movement to a standard exercise programme for patients with rotator cuff related pain: a randomised, placebo-controlled protocol trial

**DOI:** 10.1186/s12891-020-03765-6

**Published:** 2020-11-12

**Keywords:** Musculoskeletal manipulations, Mobilisation with movement, Shoulder pain, Rotator cuff, Exercise

## Abstract

**Background:**

Rotator cuff related pain (RCRP) is one of the most common sources of musculoskeletal shoulder pain affecting the general population. Conservative treatment, in the form of exercise, is considered the first line approach, nonetheless, improvements seem to be modest. One therapeutic modality that might be an adjunct to the treatment of this condition is mobilisation with movement (MWM). MWM is a pain-free manual procedure that targets restricted and painful movements, commonly seen in patients with RCRP. The purpose of clinical trial is to determine whether MWM with exercise has benefits over sham MWM with exercise in RCRP.

**Methods:**

A randomised, sham-controlled trial of 70 adults complaining of RCRP will compare the effects of MWM combined with exercise over sham MWM with exercise. Participants will be allocated to one of two groups: exercise and MWM (EG) or exercise and sham MWM (CG). Two weekly individual treatment sessions will be conducted over five weeks. All assessments will be performed by a blinded assessor. Primary outcome measures will be the shoulder pain and disability index (SPADI) and the numeric pain rating scale (NPRS), assessed at baseline, discharge and one-month follow-up. Secondary outcome measures will be active range of motion, self-efficacy and the global rating of change scale. The analyses will be conducted considering a statistically significant *p*-value ≤0.05. Normality will be assessed with the Kolmogorov-Smirnov test and homogeneity with the Levene’s test. For the primary outcome measures (SPADI and NPRS) and self-efficacy, a 2 × 3 ANOVA with treatment group (EG versus CG) and time (baseline, end of the treatment and follow-up) factors will be performed. Separate 2 × 2 ANOVA will be used for range of motion (baseline and end of the treatment). Global rating scale of change analysis will be conducted using descriptive statistics. Intention-to-treat analysis will be adopted.

**Discussion:**

As there is a paucity of longitudinal studies investigating the use of MWM in patients with RCRP, this study will help to better understand its role together with a structured exercise programme.

**Trial registration:**

Clinical Trials Registry number NCT04175184. November, 2019.

## Background

Shoulder pain is one of the most common sources of musculoskeletal pain that affects up to 20% of the population [1]. Importantly, approximately 40% of people complaining of shoulder pain will still be symptomatic six months after onset [2]. Rotator cuff related pain (RCRP) or non-specific shoulder pain is a term that includes a diversity of shoulder conditions known as: subacromial impingement syndrome, rotator cuff tendinitis/tendinopathy, rotator cuff tear, and bursitis [3, 4]. The use of a broader term is useful as the diagnostic accuracy of special orthopaedic tests have been widely criticised and are unable to identify pathognomonic sources of symptoms in people presenting with shoulder pain [5–7]. Additionally, even though diagnostic imaging is capable of identifying pathology in patients with rotator cuff related pain, correlation of these findings with the clinical presentation is questionable [8–11].

Physiotherapy has an important role in the management of rotator cuff related pain, and exercise is the main therapeutic approach when considering pain and functional restriction [12–14]. However, the improvements seem to be modest [12, 15]. A recent update of systematic reviews has suggested that adding manual therapy to exercises might offer superior short-term decrease in pain [16]. However, this finding was based on few studies with low quality level.

Mobilisation with movement (MWM) is a musculoskeletal treatment approach that focuses on improving active pain-free range of motion [17]. One of the main cardinal signs in patients suffering from rotator cuff related pain is pain on active movement. MWM incorporates a passive glide force produced by the clinician, followed by an active movement executed by the patient. Different studies have suggested positive effects of MWM over a sham procedure in patients complaining of shoulder pain [18–20], while other studies reported no such effects [21, 22]. Several methodological aspects might have influenced this discrepancy in results, such as population studied, dosage and type of MWM utilized, as well as follow-up period and outcome measures. Of particular interest here is the fact that all studies that have investigated the use of MWM in patients with shoulder pain, utilized only one form of MWM. This aspect does not explore all MWM possibilities for patients with shoulder pain [17]. Consequently, the use of MWM in patients with rotator cuff related pain deserves greater investigation. Therefore, the purpose of this study is to explore the effects of MWM applied pragmatically, reflecting usual clinical practice for this form of musculoskeletal disorder management.

## Methods

### Objectives

Due to the uncertainty in MWM effectiveness for shoulder pain, the current research aims to explore the inclusion of MWM to a 5-week exercise programme in patients with rotator cuff related pain on different functional outcome measures and pain. Additionally, a comparison will be made with a previously used sham MWM [18] to account for contextual effects of treatment procedures [23]. Furthermore, we will conduct different secondary analysis (to be published separately) exploring the effects of the interventions applied (MWM and sham MWM) on pain pressure threshold in order to verify whether the interventions used have different mechanisms of action. A further aim of this study to be published separately, is to evaluate expectation on treatment outcome, which will be investigated at baseline and during the third week of treatment.

### Trial design

This randomized, placebo-controlled, parallel study design will be conducted in two different sites with data collection at baseline, after the treatment period and at one month follow-up. The study was designed following the standard protocol items for randomized interventional trials (SPIRIT) and the results will be reported in accordance with the consolidated standards of reporting trials (CONSORT) guidelines for randomized trials [24].

### Study settings

The study will occur in two different locations, at the physiotherapy laboratory 1 at *Faculdades Integradas de Taquara* and a private practice (*Clínica Albrecht*). The Recruiment process and flow through study is depicted in Fig. 1.

**Fig. 1 Fig1:**
[figure not shown]
Recruitment process and flow through study

### Eligibility criteria

Inclusion and exclusion criteria can be found in Table 1. Criteria utilized are similar to studies investigating the use of manual therapy treatment procedures with or without exercise in patients with rotator cuff related pain [18, 19, 25–28].

**Table 1 Tab1:** Inclusion and exclusion criteria

Inclusion criteria	Exclusion criteria
1. Age 18–65 years.	1. Shoulder pain following a traumatic event.
2. Unilateral shoulder pain of atraumatic origin.	2. History and clinical presentation compatible with complete rotator cuff and/or biceps brachii rupture.
3. Scoring at least 3 out of 10 on a numeric pain rating scale.	3. Adhesive capsulitis.
4. Symptoms lasting more than 6 weeks.	4. History of dislocation.
5. Pain on active shoulder movement.	5. Glenohumeral osteoarthritis.
6. Pain provoked by at least three of the following tests: Hawkins-Kennedy, Neer, Painful arc, Empty/full can and Resisted external rotation.	6. Cancer
7. Patients referred by a shoulder specialist with diagnosis of rotator cuff injury (tendinitis/tendinosis), subacromial impingement syndrome, bursitis, subacromial pain, that fulfill the criteria above.	7. Systemic, local or auto-immune inflammatory conditions.
	8. Previous shoulder or neck surgery or fracture.
	9. Familiar pain provoked by neck movements.
	10. Presence of radicular signs.
	11. Use of corticosteroids over the past six months.
	12. Diagnosis of fibromyalgia.
	13. Clinical depression.
	14. Participants under treament for his/her shoulder condition over the last 3 months.

### Interventions

The treatment phase starts after the participant is deemed eligible and agreed to participate voluntarily and signed a structured consent form. After randomization, participants will be allocated to one of two groups described below. The treatment phase will last 5 weeks.

### Experimental group (EG)

#### Exercise programme

The list of exercises to be conducted in all therapeutic sessions (Additional file 1) was constructed based on previous studies and following recommendations commonly reported in the literature [26, 29–31].Two to three sets of 10 to 15 repetitions will be performed using elastic therapeutic bands and dumbells. Three repetitions of 15 s of the stretching exercises will be performed after the strengthening exercises. Exercise progression load will be individually based and managed in a way that a value of a maximum pain score of 5/10 on a verbal rating scale (0 - no pain and 10 - maximal tolerable pain) should be observed during the execution of the exercises. If no such symptom occurs, a score of 6 on a BORG scale (0 – rest and 10 – extremely strong) will be applied. Therefore, during the treatment sessions, the load utilized (dumbells or elastic bands) will be adjusted according to the perception of symptoms. On the first session, 2 sets of 10 repetitions respecting the aforementioned symptoms will be conducted. In this way, participants will become familiar with the exercise programme and this will also inform on immediate symptom reproduction after the session. On the second session, 3 sets of 10 repetitions will be performed. Then, every week after that, 3 sets of 15 repetitions will be conducted with the adjusted load (same load, more load or less load) based on the perception of symptoms. An interval of 45–60 s will be provided between sets and exercises. Participants will be informed about the importance of increasing the load, while still respecting symptoms. In addition, if symptoms provoked by the exercise programme are still present 24 h later, the exercise load will be diminished until this no longer occurs.

#### Mobilisation with movement (MWM)

The participant and physiotherapist will decide on one active shoulder movement more functionally relevant to the individual. Following this, up to four attempts of MWM will be applied to different joints (cervical spine, thoracic region, scapulothoracic, as well as glenohumeral and acromioclavicular joints) and / or in different positions (standing, sitting or lying), in order to identify one particular MWM that improves significantly the shoulder movement previously selected [17]. The shoulder movement will be conducted to the onset of symptoms, should they occur. Then, one set of six to 10 repetitions will be applied repeating the same movement through pain-free range.This process of pragmatically applying MWM will be respected in every session, but from the second session onwards, two to three sets of 10 repetitions will be applied, with an interval of sixty seconds between sets. In case of failure to identify a MWM that improves the movement significantly, the patient will decide which one seems best and one set of six repetitions will be performed to the onset of discomfort.

### Control group (CG)

#### Exercise programme

Exactly the same as the experimental group and conducted in the same way.

#### Sham mobilisation with movement (MWM)

The participant and physiotherapist will decide on one active shoulder movement that is more functionally relevant to the individual. Following this, a sham MWM [18] will be applied and the movement previously selected will be repeated six to ten times in the first consultation. Briefly, the sham condition simulated the MWM procedure with a different hand positioning. The clinician, standing contralaterally to the treated shoulder, will place one hand over the superior aspect of the pectoralis major muscle and the other over the scapula, both hands will make skin contact only without any significant pressure. The participant will be informed that he or she should move to the onset of symptoms, if they occur.This process will be respected in every session, but from the second session onwards, two to three sets of 10 repetitions will be applied, with an interval of sixty seconds between sets. However, in case the sham MWM fails to improve the movement significantly, one set of six repetitions will be performed only**.**

### Outcome measures

#### Primary outcome measures

##### Shoulder pain disability index (SPADI)

SPADI is a self-reported questionnaire that contains 13 different items. There are two domains: pain (5 items) and functional activity (8 items). Each item ranges from 0 (no pain / no difficulty) to 10 (worst imaginable pain / so difficult that requires help). This questionnaire is a valid and well established instrument that helps to discriminate those responding or not to a certain treatment [32]. A reduction of 8–13 points has been reported as being clinically significant [33]. The Brazilian validated version of SPADI will be used [34] at baseline, end of the treatment period, and the final follow-up.

##### Numeric pain rating scale (NPRS)

A NRPS ranging from 0 (no pain) to 10 (worst imaginable pain) is used to measure pain intensity. Scores will be recorded for resting pain, night pain and pain during movement, all related to the previous 24 h. Decreases in pain levels between 1.1 and 2.2 points or a reduction of 32–34% have been reported in the literature as being clinically significant [26, 35]. The scale will be applied at baseline, end of the treatment period and the final follow-up.

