### Sample size

In order to calculate the number of subjects to be included in this study an alpha value of 0.05 and power of 80% was chosen together with a minimal clinically important difference of 10 points on the SPADI scale with standard deviation of 13.5 points [26]. An initial number of 28 participants in each group was required based on this calculation. With an estimated 20% loss to follow-up, we planned to recruit a total of 70 subjects (35 in each group).

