### Statistical analysis

Data will be analysed using the Statistical Package for Social Science software (SPSS v.20, Inc., Chicago, USA). The analyses will be conducted considering a statistically significant *p*-value ≤0.05. Data normality of the study will be assessed with the Kolmogorov-Smirnov test and homogeneity with the Levene’s test. The results will be reported as the mean with corresponding 95% confidence interval. Intention-to-treat analysis will be conducted so that all patients are analysed within their group allocation. Drop-outs and their reasons will be informed. All data input will be kept in two different files (double data entry) that will be updated every week by a research assistant.

A two-way analysis of variance will be conducted to assess between and within groups differences. For the primary outcome measures (SPADI and NPRS) a 2 × 3 ANOVA with treatment group (EG versus CG) and time (baseline, end of the treatment and follow-up) factors will be performed. Separate 2 × 2 ANOVA will be used for ROM (baseline and end of the treatment period), and a 2 × 3 ANOVA will be conducted for self-efficacy (baseline, end of the treatment period and follow-up). Additionally, appropriate post-hoc tests (Bonferroni) will be used if prior analysis indicates significant differences. GROC analysis will be conducted using descriptive statistics and participants will be classified according to treatment success. Those reporting + 5 or more will be classified as successful. Within groups differences will be calculated at the end of the treatment period and follow-up, and effect sizes will be calculated using Cohen effect size (0.2–0.5: small effect, 0.5–0.8: moderate effect, 0.8 or more: large effect size).

A second study will explore changes in expectation throughout treatment descriptively and whether those differences are associated with SPADI, NPRS and group allocated. Therefore, an ANCOVA will be conducted to analyze the influences of covariates (expectation and self-efficacy) on SPADI and NPRS. A separate 2 × 3 ANOVA will be used to examine PPT measurements in the three different body areas. Post-hoc tests (Bonferroni) will be used if prior analysis indicates significant differences.

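### SPADI and NPRS are unranked primary outcomes, each judged at p ≤ 0.05 with no rule covering them jointly, so the chance of a false primary finding is about 8–10% (NPRS as one outcome) or 11–18.5% (three NPRS scores)

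*Protocol article*

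**What the plan says.** All references are to the protocol article.

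- **Primary set.** The Abstract (Methods) and the Outcome measures section name SPADI and NPRS as primary and rank neither. The registration data set (Table 2) lists function and pain.
- **NPRS is three scores.** Under Numeric pain rating scale: "Scores will be recorded for resting pain, night pain and pain during movement". No composite or lead score is named.
- **Visits.** Of the NPRS: "The scale will be applied at baseline, end of the treatment period and the final follow-up". SPADI follows the same schedule.
- **Test.** Under Statistical analysis: "For the primary outcome measures (SPADI and NPRS) a 2 × 3 ANOVA with treatment group (EG versus CG) and time" as factors.
- **Threshold.** The analyses are run "considering a statistically significant *p*-value ≤0.05".
- **Correction.** Bonferroni post-hoc tests follow if the ANOVA is significant. The article describes no other adjustment.
- **Sizing.** Under Sample size, the basis is a "minimal clinically important difference of 10 points on the SPADI scale" with SD 13.5, alpha 0.05 and 80% power. This gives 28 per group, raised to 35 per group (70 in total) for 20% loss. NPRS has no calculation.

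**The concern.** When a trial has more than one primary outcome, its plan has to say how they combine: all must succeed, any one suffices with alpha shared, or they are tested in a set order. This article does none of these. It does set the list of primary outcomes, the threshold for each and one correction that stays inside a single outcome. Taken together, these allow significance on any one primary score to be reported as a positive trial.

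The purpose of the trial is to decide whether adding MWM to exercise is better than adding sham MWM. If MWM adds nothing, a significant result on night pain alone could still be presented as a primary success, and readers would credit it with a 5% error rate that it does not have. The outcome that carried the sample size might show nothing.

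**Working it through.** **Inputs from the article.** Two primary instruments, or four scores if the three NPRS ratings are analysed separately (SPADI; NPRS at rest, at night and on movement). One 2 × 3 ANOVA per outcome. Threshold 0.05. Sizing: difference 10, SD 13.5, alpha 0.05, power 80%, loss 20%.

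**Assumed.** Two-sided testing, because sidedness is not stated. Correlation between scores from 0 to 0.8, because the article gives none.

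**Step 1: reproduce the sample size.**
n per group = 2 × (1.960 + 0.842)² × 13.5² / 10² = 2 × 7.85 × 1.8225 ≈ 28.6, so 29 against 28 stated. Power at 28 per group is about 79% (normal approximation) or 78% (t test). Allowing for loss, 28 / 0.8 = 35 per group, 70 in total. The sizing reproduces within rounding and is not at issue.

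**Step 2: error with one test per outcome.**
If the tests are independent, the chance of at least one false finding is 1 − 0.95^k.
- k = 2: 1 − 0.95² = 9.75%
- k = 4: 1 − 0.95⁴ = 18.5%

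For correlated scores, simulated under no effect with equal correlation between scores:

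| Correlation | 2 instruments | 4 scores |
|---|---|---|
| 0 | 9.7% | 18.5% |
| 0.3 | 9.4% | 17.3% |
| 0.5 | 9.1% | 15.5% |
| 0.7 | 8.3% | 13.0% |
| 0.8 | 7.9% | 11.4% |

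Simulating the group-by-time interaction itself, with 28 per arm and correlation 0.5 between visits, gives nearly the same: 9.8% falling to 7.8% for two outcomes, and 18.6% falling to 11.3% for four.

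**Step 3: dependence on the decision rule.** The article does not say which ANOVA effect decides success. For four scores, over correlations 0 to 0.8:
- Group effect or interaction, either counting as a finding: about 21–34%.
- Either effect significant, plus a Bonferroni-significant group difference at a visit (each visit at 0.025): about 8–13%.
- Interaction significant, plus a Bonferroni-significant group difference in change from baseline: about 8–13%.
- Interaction significant, plus a Bonferroni-significant group difference in the raw score at a visit: about 2–4%.

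Only the last rule stays below 5%.

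**Step 4: cost of dividing alpha instead.** Using the Step 1 formula:
- Alpha 0.025 (two instruments): 35 per group; 35 / 0.8 = 43.75, so 44 per group and 88 in total. Power for SPADI at 28 per group is about 70%.
- Alpha 0.0125 (four scores): 41 per group; 41 / 0.8 = 51.25, so 52 per group and 104 in total. Power for SPADI at 28 per group is about 61% (58% by t test).

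**The case against.** **Visits.** A reader might infer that four scores at two visits make eight unadjusted tests, with error 1 − 0.95⁸ = 34%. The article does not support this. Both visits enter one ANOVA per outcome, and the post-hoc comparisons are gated by that ANOVA and Bonferroni-corrected. The problem lies across outcomes.

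**Four scores.** The article names two primary measures. It says that three NPRS ratings are recorded, not that each has its own primary ANOVA. This is fair, and it is why the two-instrument figures stand beside the four-score figures. Even on that reading the rate is 8–10%.

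**Independence.** SPADI has a pain domain, and the NPRS ratings concern the same shoulder over the same 24 hours, so correlation is likely. This stands: the lower parts of the ranges are the more plausible. They remain above 5%.

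**The strict rule.** If success needed both a significant interaction and a Bonferroni-significant raw difference at a visit, error would be about 2–4%. This stands as arithmetic, but the article does not adopt that rule.

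**An unseen analysis plan.** Which effect or visit decides, and how the NPRS ratings are handled, may be settled elsewhere, and their absence alone is no finding. But the article does fix the primary set, the threshold and the one correction, and these do not control error across the outcomes.

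**Floor effects.** Entry requires "Scoring at least 3 out of 10 on a numeric pain rating scale" without saying which rating, so a reader might infer that rest and night pain start too low to improve. The article gives no baseline values to support this. A floor would reduce power; it would not raise false positives.

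**Sizing on one outcome.** Sizing on SPADI alone is not an error. It matters here only because it shows which outcome the trial was built on.

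**Conclusion.** The concern holds as a matter of multiplicity across the primary outcomes. With one test per outcome, the chance of at least one false primary finding is about 8–10% if NPRS is one outcome and about 11–18.5% if its three scores are tested separately. These figures assume two-sided tests, no true effect on any outcome, and correlations from 0.8 down to 0. They would fall below 5% only under a strict success rule that the article does not state. The claim does not extend to unadjusted testing at each visit, and the sample size calculation is not wrong. Because a change of wording resolves it with no change in numbers, it is a cheap improvement.

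**What to change.** 1. Name SPADI as the single primary outcome, with one between-group contrast at one visit. End of treatment is a natural choice, but the Sample size section names no visit, so the sponsor should fix it.
2. Test NPRS during movement next, in fixed sequence, and only if SPADI reaches p ≤ 0.05.
3. Report NPRS at rest and at night, and the results at the other visit, as secondary, with 95% confidence intervals and no confirmatory claim.

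This holds the error over the confirmatory tests at 5%. If MWM has no effect on SPADI, a false claim requires the SPADI test to fail at its 5% level. If MWM does affect SPADI, the only remaining false claim is on NPRS, also tested at 5%.

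**Cost.** Wording in the protocol and the registration entry, settled before any comparison by group. The target stays at 70 and SPADI power is unchanged. The downside is that a claim on pain becomes conditional on SPADI. Dividing alpha would avoid that condition, but it needs 88 or 104 participants to restore 80% power, so it is not proposed.
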